### Participating agencies and staff

HIV infection rates in California rank third in the U.S.; Los Angeles and Alameda Counties have the largest concentrations of African Americans in California and, accordingly, the highest proportion of African American HIV/AIDS cases [39]. A recent report indicates that the City of Oakland (Alameda County) has the highest and most rapidly growing incidence rate of diagnosed and undiagnosed HIV in the country and is struggling with what has been referred to in the news as an ‘unstoppable epidemic’ [40]. The State of California and local stakeholders have responded to this challenge with active prevention programs such as Get Screened Oakland [41,42].

We recruited ten HIV/AIDS CBOs in Los Angeles and Alameda Counties to serve as study sites. All of these agencies are well-established CBOs that serve large numbers of HIV-infected African Americans. In fact, these CBOs expressed particular interest in offering services to couples because they currently do not provide such services. These agencies were identified as having met seven key elements identified in the literature as important in determining agencies’ readiness to implement a new intervention [43]. These include: a respected local community advocate; strong administrative support; formal organizational commitments and stability; commitment of necessary resources to incorporate the program into existing services; program credibility within the community; adequate facilitators/staff; and potential for the program to be self-sustaining or willing to seek additional funding. In addition, all of the agencies have adequate space for conducting private assessment and group sessions.

Approximately 200 staff members from these agencies (~20 per agency) will complete the staff- and organizational-level measures described below. A subset of these individuals (approximately 50 ‘key stakeholders,’ including agency administrators, site coordinators, and facilitators) who are directly involved in implementation will complete semi-structured interviews.

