### Measures to be completed by staff

An electronic Staff Survey will capture basic demographics of staff (~20 per agency) including education level and professional experience. The 50-item Evidence-Based Practices Attitudes Scale (EBPAS) [50] will be used to assess staff attitudes toward evidence-based practices. The widely used Maslach Burnout Inventory (MBI; Maslach) [51] will be used to assess staff experience of workload. Subscales from the TCU Survey of Organizational Functioning (TCU SOF) [52] will be used to assess motivational factors, program resources, staff attributes, and organizational readiness. All subscales of the SOF have demonstrated good internal consistency and validity [53].

In addition to these structured measures, semi-structured interviews will be conducted with a subset of key stakeholders (approximate n = 50; five per agency). Process-focused interviews will include questions about feasibility, satisfaction, perceived fidelity, barriers, desired revisions, perceived cost-effectiveness, and expectations for sustainability. Sustainability-focused interviews will include similar questions, but will refer to the sustainability period and their satisfaction with and future expectations of the utility and cost-effectiveness of Eban II as a long-term option for agencies’ usual menu of services.

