### Sample size calculation and power analyses

Sample size calculation and power analyses were conducted at both the agency- and couple-levels to ensure that we have sufficient statistical power for all analyses. At the agency level, the power analysis was based on the comparisons of key measures from providers (*e.g.*, provider attitudes toward evidence-based practices). From the 10 selected agencies, we will collect data from 100 non-clerical staff (10 providers per agency) in order to provide sufficient power to examine the within- and between-agency variation. With a type I of 0.05, type II error of 0.2 (or power of 80%), intra-agency correlation at 0.15 level, 100 raters from the 10 agencies will enable us to detect an effect size as small as 0.9 in standard deviation unit for measures from staff [65,66]. Non-parametric and parsimonious models will be used to accommodate the limitation of a relatively small number of agencies.

At the couples level, calculations were carried out based on the comparison of key outcome measures of incidents of unprotected sex and an increase in the proportion of condom use (*i.e.*, the number of times condoms were used during intercourse divided by the number of times sexual intercourse is reported) between intervention and waitlist control. With a repeated measures design, type I error 0.05, type II error 0.20, intra-couple correlation 0.4, the mean number of available repeated measures 2.5 (from baseline, post and three-month measurements), and a 2:1 ratio of intervention and waitlist control, a total of 174 couples would allow us to detect an effect size as small as 0.30 in standard deviation unit for number of unprotected sexual intercourse acts [65,67]. Thus, our planned sample of 180 couples provides sufficient power.

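### The staff sample is about 200 in two sections but 100 in the power section, and the 0.9 SD stated for 100 staff takes no account of there being only 10 agencies

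*Protocol article*

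**What the plan says.** The section on participating agencies and staff states: "Approximately 200 staff members from these agencies (~20 per agency) will complete the staff- and organizational-level measures described below". The section on staff measures repeats the per-agency figure: "An electronic Staff Survey will capture basic demographics of staff (~20 per agency"). It lists a scale of attitudes toward evidence-based practice among the instruments.

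The sample size section gives half that number: "we will collect data from 100 non-clerical staff (10 providers per agency"). Its example of a key measure is again provider attitudes toward evidence-based practice. Its inputs are "With a type I of 0.05, type II error of 0.2 (or power of 80%), intra-agency correlation at 0.15 level", and its result is that "100 raters from the 10 agencies will enable us to detect an effect size as small as 0.9 in standard deviation unit". On what is compared, it says only that "the power analysis was based on the comparisons of key measures from providers". It gives no grouping of agencies, split, sidedness or degrees of freedom.

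The same section acknowledges that the agencies are few and promises non-parametric and parsimonious models. The analysis plan for aim two repeats this and gives Mann-Whitney as its example.

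**The concern.** There are two linked problems.

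First, the number of staff supplying the same kind of data differs by a factor of two. The sample size section speaks of collecting data from 100, not of analysing a subset. The only subset of the 200 that the article names is the group of about 50 key stakeholders who are interviewed. Non-clerical providers may be part of the wider staff, but the reader has to guess.

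Second, the detectable effect is quoted for 10 clusters. If the factor compared is a characteristic of the agency, the evidence comes from 10 agency means, however many staff respond. A calculation that inflates the variance for clustering but keeps a normal reference distribution, or counts degrees of freedom from staff, overstates power when clusters are so few.

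At stake is the power statement behind the quantitative part of aim two, a primary implementation aim. The section says its calculations ensure sufficient power for all analyses.

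**Working it through.** **Inputs from the sample size section:** 10 agencies, m = 10 staff per agency, intra-agency correlation 0.15, alpha 0.05, power 80%, stated effect 0.9 SD. The alternative m = 20 comes from the two staff sections.

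**Assumptions, since the article is silent:** a two-group comparison between agencies, two-sided, split 5 v 5, with 4 v 6, 3 v 7 and 2 v 8 as the range.

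**Step 1: reproduce the stated figure.**
- Design effect = 1 + (10 − 1) × 0.15 = 2.35. Effective sample = 100 / 2.35 = 42.6.
- Variance of an agency mean = 0.15 + 0.85/10 = 0.235.
- SE of the difference at 5 v 5 = √(0.235 × (1/5 + 1/5)) = √0.094 = 0.307 SD.
- Detectable effect, normal = (1.96 + 0.84) × 0.307 = 0.86 SD. Power at 0.9 SD = Φ(0.9/0.307 − 1.96) = 83.5%.
- A t test on the effective sample (about 40.6 df) gives 0.88 SD and 81.7%. At 4 v 6 it gives 0.90 SD and 80.2%.

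The stated 0.9 SD is therefore reproduced.

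**Step 2: is this a between-agency contrast?** Two equal staff groups formed within agencies would give 2.80 × √(0.85 × (1/50 + 1/50)) = 0.52 SD. The stated 0.9 SD is far from that and close to the between-agency result. This points to a between-agency comparison but does not prove it.

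**Step 3: same variances, reference distribution from 10 agencies.** Degrees of freedom = 10 − 2 = 8. Power is from the noncentral t, two-sided 0.05. With m = 20, the variance of an agency mean is 0.15 + 0.85/20 = 0.1925, and the SE at 5 v 5 is √(0.1925 × 0.4) = 0.277 SD.

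| Split | 10 per agency, normal | 10 per agency, t on 8 df | 20 per agency, normal | 20 per agency, t on 8 df |
|---|---|---|---|---|
| 5 v 5 | 83.5% (0.86) | 73.0% (0.98) | 90.0% (0.78) | 81.0% (0.89) |
| 4 v 6 | 82.0% (0.88) | 71.3% (1.00) | 88.8% (0.79) | 79.4% (0.91) |
| 3 v 7 | 76.7% (0.94) | 65.6% (1.07) | 84.4% (0.85) | 74.0% (0.97) |
| 2 v 8 | 65.1% (1.07) | 54.1% (1.23) | 73.7% (0.97) | 62.5% (1.11) |

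Entries are power at 0.9 SD, with the effect detectable at 80% power, in SD, in brackets.

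**Step 4: the test given as the example.** Exact Mann-Whitney on agency means, 5 v 5, two-sided, 20,000 simulated data sets with a true difference of 0.9 SD: power about 62% with 10 per agency and about 70% with 20.

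**Step 5: sensitivity to sidedness.** One-sided at 0.05 on 8 df, 5 v 5: 84.9% with 10 per agency.

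**The case against.** The strongest reply is that the authors made no error. Their figure follows from their own inputs by the standard formula, and the shortfall appears only after adding choices that the article does not state: two groups of agencies, a two-sided test and 8 df. A one-sided test on the same 8 df would pass. A contrast of staff within agencies would not be confined to 8 df. The article also admits that the agencies are few, and much of aim two is descriptive or qualitative. Finally, a provider subset of all staff is a natural reading, and the mismatch errs on the safe side: if about 200 respond, the authors' own method gives 90% power at 5 v 5.

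Much of this stands. A reader might infer from the shortfall that 0.9 SD was miscalculated; step 1 shows that it was not. A reader might also infer that the choice between 100 and 200 staff decides whether 0.9 SD holds. That is true only for a two-sided 8-df t test at exactly 5 v 5. By the standard formula at 5 v 5 or 4 v 6, both numbers suffice. On 8 df at 4 v 6 or 3 v 7, or with Mann-Whitney on agency means at 5 v 5, neither does.

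What does not stand is the idea that the acknowledgement settles the matter. The article plans methods suited to few agencies but quotes a detectable effect that matches a calculation without that allowance. Non-parametric testing on agency means lowers power further. Nor does the subset reading reconcile the numbers, because the article never says it.

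**Conclusion.** The contradiction in staff numbers is plain on the face of the document: about 20 per agency in two sections, 10 per agency in the third, with no reconciling sentence.

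The power statement is correct by the formula it appears to use but optimistic for the comparison it appears to describe. For a two-sided comparison between agencies, 10 staff per agency give at best 73% power at 0.9 SD, not 80%, and 80% power needs 0.98 SD. Unequal splits lower power to between 71.3% (4 v 6) and 54.1% (2 v 8), and Mann-Whitney on agency means at 5 v 5 gives about 62%. Twenty per agency only just repairs this, and only at 5 v 5 with the t test.

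These figures rest on the stated correlation of 0.15 and on the assumed two-group, between-agency, two-sided comparison. They do not show that aim two is unworkable. They show that its stated power cannot be relied on until the comparison is specified. The point is worth correcting because it is cheap to correct.

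**What to change.** 1. Use one staff number throughout: either about 200, or 100 providers named explicitly as the analysis subset of the roughly 200 surveyed.
2. State what the 0.9 SD refers to: the groups compared, the expected split of agencies, the sidedness and the test.
3. Restate the detectable effect or the power on a small-cluster basis that matches the planned test. For a two-sided 8-df t test with a 5 v 5 split, the detectable effect is about 0.98 SD with 10 per agency or 0.89 SD with 20. These values apply only if that split is the one planned; unequal splits or a non-parametric test need larger effects.
4. If the regression adjusts for agency size, staff number and budget, note that each agency-level covariate uses further degrees of freedom.

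The cost is a few sentences and one recalculated figure. No change to recruitment or data collection is needed if about 200 staff are already to be surveyed.

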### Data analysis plan

#### Specific aim one

Qualitative data will document how we assist the 10 CBOs to implement and sustain the intervention. As a broad implementation aim, there are no hypotheses associated with this aim. Instead, the focus will be on describing the process of assisting the CBOs with implementation and sustainability. This description and summary will be generated from interviews and notes from the monthly SCIN calls, along with other qualitative data that is gathered throughout the study.

#### Specific aim two

To document the implementation process and identify barriers and facilitators to adoption, fidelity, and sustainability, we will utilize a variety of analytic approaches. First, marginal distributions of each of the measures at the agency level (*e.g.*, intervention cohorts completed, provider attitudes, etc.) will be obtained. For continuous measures (*e.g.*, the number of facilitator teams trained), we will calculate the range, mean, median, quartiles, and standard deviations. For categorical measures (*e.g.*, fidelity to core elements), frequency distributions and mode will be obtained. An ordinal measure that reflects the number of intervention groups conducted at each agency will be created, which will be used to link with the number of intervention cycles completed and to test the dose–response of the intervention. For performance measures (*e.g.*, satisfaction) obtained from providers at the CBOs, analyses will be conducted, and within and between agency variations will be examined. Non-parametric methods (*e.g.*, Mann Whitney test) will be used to accommodate the relative small sample size of agencies. Rigorous statistical tests will be conducted in three steps: marginal distributions of the number of intervention cycles completed will be obtained; two-way table chi-squares or analysis of variance will be used to evaluate the relationships between the categories of number of intervention cycles completed and the extent of successful implementation, which is measured by an array of variables (*e.g.*, number of couples served, degree of fidelity, level of satisfaction with the intervention, etc.); and multivariate analyses will be conducted through regression models to examine the relationships between provider measures and number of intervention cycles completed, controlling for other agency characteristics such as agency size, number of staff, size of budget, etc.

Data regarding acceptability, barriers, and facilitators will be derived from interviews and implementation-focused evaluation measures. As we are examining implementation in 10 large, diverse CBOs, barriers and facilitators will likely vary by agency. The qualitative data will provide the research team with extensive information about acceptability, barriers, and facilitators. In addition, we will examine the facilitator and couples’ satisfaction ratings to characterize acceptability of the intervention. These ratings will be compared both within and across agencies. Potential determinants of adoption and fidelity include but are not limited to training factors, competency at delivering the intervention, types of facilitators (*e.g.*, whether agencies used their own staff as facilitators or used the floating facilitator team), couple ‘mix’ in a given cohort, retention, and satisfaction. All of these factors will be examined when characterizing fidelity across agencies. In addition, based on interviews with facilitators and clients, we will remain open to other determinants that may emerge during implementation. There are several possible determinants of sustainability. We hypothesize that sustainability will be achieved in agencies that have their own trained staff facilitators who deliver the intervention with fidelity and who had positive experiences with the intervention during the implementation phase. To test this hypothesis, we will perform analyses in two levels: (1) Bivariate analyses between sustainability and characteristics of the CBOs and staff. The Pearson Chi-square will be used to test association. ANOVA will be used to test the means of the continuous measures (*e.g.*, ‘the number of agencies that continue to implement Eban II with fidelity’) across the different levels of a categorical measure (‘Does your agency have specific services for high-risk or HIV-positive couples? Yes/no’) at each time point of data collection; (2) Longitudinal analyses for long-term effects. Generalized linear mixed models (GLMM) [67,68] will be used to evaluate the relationship between sustainability and characteristics of the CBOs. GLMM cannot only model global fixed effects (*e.g.*, the number of full-time staff), but also can model random variation (*e.g.*, change over time of individual agency), which is particularly useful.

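### Aim two does not fix the unit of analysis for its tests of staff measures against agency-level factors, and neither reading matches the power statement: pooling staff gives 20–32% false positives, agency summaries give about 61–73% power

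*Protocol article*

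**What the plan says.** Under Sample size calculation and power analyses, the agency-level calculation rests on provider measures: "we will collect data from 100 non-clerical staff (10 providers per agency", with "intra-agency correlation at 0.15 level", type I error 0.05 and power 80%. It concludes that the study can "detect an effect size as small as 0.9 in standard deviation unit for measures from staff". Participating agencies and staff gives a larger number: "Approximately 200 staff members from these agencies (~20 per agency) will complete the staff- and organizational-level measures".

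The tests are named under Specific aim two. Directly after a sentence on performance measures obtained from providers comes "Non-parametric methods (*e.g.*, Mann Whitney test) will be used to accommodate the relative small sample size of agencies". Chi-square or ANOVA then relates the number of cycles completed to implementation success, and regression relates provider measures to cycles completed. For sustainability the first step is "Bivariate analyses between sustainability and characteristics of the CBOs and staff. The Pearson Chi-square will be used to test association", with ANOVA for continuous measures.

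Cycles completed has one value per agency, and the Sustainability section defines sustainability per agency. None of these analyses is given an agency term. A generalized linear mixed model follows, but for sustainability against characteristics of the agencies. Only Specific aim three says how intra-class correlation from agency and staff will be handled.

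**The concern.** The power section treats staff of one agency as correlated. The named tests, applied to individual staff, assume independence. A rank test relaxes the distributional assumption, not the independence assumption, so it would not remedy a small number of agencies if staff are the rows. If agencies are the rows, independence is respected, but the power statement then no longer describes the test.

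Determinants of fidelity and sustainability are a primary implementation aim, and the sustainability hypothesis is tested first by these bivariate analyses. Depending on an unstated choice, that evidence carries either an inflated false-positive rate or less power than claimed.

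**Working it through.** **Inputs.** From the power section: 10 agencies, 10 staff per agency, correlation 0.15, type I error 0.05, power 80%, detectable effect 0.9 SD. From Participating agencies and staff: about 20 staff per agency as the alternative. Assumed, because not stated: two-sided tests, equal numbers per agency, and a factor that varies only between agencies, with the 10 agencies split 5:5 (range to 2:8).

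**1. Reproduce the plan's 0.9 SD.**
- Design effect = 1 + (10 − 1) × 0.15 = 2.35.
- Detectable effect = (1.960 + 0.842) × √[2.35 × (1/50 + 1/50)] = 2.802 × 0.3066 = 0.86 SD.
- Using t with degrees of freedom from the effective sample size gives 0.88 (5:5) or 0.90 (4:6).
- Without the design effect it is 2.802 × √(1/50 + 1/50) = 0.56 SD.

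The stated 0.9 therefore reproduces only with the 0.15 applied: staff-level data, discounted for clustering.

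**2. Rows are individual staff, clustering ignored.** The true variance is the design effect times what the test assumes, so the rejection rate under no effect is 2 × [1 − Φ(1.96/√DE)].

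| Correlation | Staff per agency | DE | Formula | Simulated Mann-Whitney, 5:5 |
|---|---|---|---|---|
| 0.15 | 10 | 2.35 | 20.1% | 20.1% |
| 0.15 | 20 | 3.85 | 31.8% | 31.6% |
| 0.05 | 10 | 1.45 | 10.4% | 9.9% |
| 0.05 | 20 | 1.95 | 16.0% | 15.5% |

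The simulation used 10,000 replicates. At correlation 0.15, over splits 5:5 to 2:8, Mann-Whitney rejected 19.2–20.1% (10 per agency) and 30.8–32.1% (20 per agency). Pearson chi-square on a binary staff characteristic with correlation 0.15 rejected about 20–22% and 32–34%. If 0.15 instead belongs to a latent score cut at its median, chi-square gives about 16% and 25%.

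**3. Rows are agency summaries.**
- Type I error: exact Mann-Whitney rejected 2.8–4.7% in simulation. At 5:5 its attainable two-sided level is 8/252 = 3.2%.
- Variance of an agency mean = 0.15 + 0.85/10 = 0.235.
- Standard error of the 5:5 difference = √[0.235 × (1/5 + 1/5)] = 0.3066.
- t test on 8 degrees of freedom: noncentrality 0.9/0.3066 = 2.94, power 73%. The effect detectable with 80% power is 0.98 SD.
- Exact Mann-Whitney on 5 versus 5 normally distributed agency means, true difference 0.9 SD: simulated power 61% (40,000 replicates).
- With 20 staff per agency the variance is 0.15 + 0.85/20 = 0.1925. The t test then has 81% power and the exact Mann-Whitney about 69% (same simulation).

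The standard error is the same in steps 1 and 3. The difference in power comes from the degrees of freedom (8, set by the number of agencies) and, for the rank test, from its coarse attainable level.

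**The case against.** A reader might infer that the plan pools staff as independent and so will reject 19–33% of true null hypotheses. The documents do not support that. No sentence says staff are the rows. Mann-Whitney is justified by the small number of agencies, which suits a test on about 10 agency values. Specific aim two opens by listing provider attitudes among measures at the agency level, and its regressions adjust for other agency characteristics, which suggests that provider measures may enter as agency values. Sustainability is an agency outcome, and the example grouping question is about the agency. The article also says that variation within and between agencies will be examined. The inflation is therefore conditional on pooling, on a factor that varies between agencies, and on the size of the correlation; its upper end needs 20 rather than 10 staff per agency. All of this stands.

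It can also be said that the row unit is a detail an article leaves to a fuller plan. This answers only part of the point. The article chose the tests and gave a reason, and it powered the comparison on 100 individual raters with a clustering discount. The agency-level reading fits poorly with that calculation and with a chi-square on staff characteristics. If adopted, it does not deliver the stated 80% power at 10 staff per agency. It would also leave a Pearson chi-square with 10 agencies in at least four cells, an average of at most 2.5 per cell, which calls for an exact test.

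**Conclusion.** The point holds in conditional form. Aim two leaves open whether staff or agencies are the unit for its Mann-Whitney, chi-square, ANOVA and regression analyses against agency-level variables, and neither choice agrees with the power section.

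- Staff as rows, unadjusted: type I error about 20% (10 per agency) to 32% (20 per agency) at correlation 0.15, and about 10–16% at 0.05.
- Agencies as rows: type I error about 2–5%, but with 10 staff per agency at 5:5 about 61% power (exact Mann-Whitney) or 73% (t test on agency means) for 0.9 SD.

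The figures rest on two-sided 5% tests and equal numbers of staff per agency. The power figures also assume normally distributed agency means and fall with less even splits: the t test has 71% at 4:6 and 54% at 2:8. With about 20 staff per agency the t test on agency means does reach 80% at 5:5; the exact rank test does not. The inflation does not apply in this form to factors that vary among staff within an agency.

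**What to change.** Under Specific aim two, state that any comparison across agency-level categories, including cycles completed and sustainability, uses one of:

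- a mixed model with a random agency intercept and small-sample degrees of freedom; or
- one summary per agency, with an exact or permutation test over the 10 agencies.

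State also that staff-level Mann-Whitney, Pearson chi-square, ANOVA and regression without an agency term will not be used for such inference. In the power section, restate the detectable effect for the chosen method and for the number of staff per agency actually expected. At 10 per agency and a 5:5 split it is about 0.98 SD for a t test on agency means, and larger for an exact rank test.

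The cost is analysis wording. Some nominally significant results would be lost, and the detectable effect becomes slightly less favourable. The Trial status section says that data cleaning and analysis have not commenced, so the change can still be prespecified.

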We operationalize ‘successful implementation’ [36] as a combination of number of couples served (minimum of 18 couples per agency), three completed cycles of the intervention, delivery of the intervention with high fidelity, and high level of satisfaction with the intervention. As noted above, we will also be studying sustainability and cost effectiveness of the intervention for couples. Staff and organizational characteristics will be assessed at all participating CBOs in the first year, and engagement and training will be priorities. Following successful training, implementation of Eban II will commence in two randomly selected CBOs in the first year. The remaining eight CBOs will be phased in randomly with refresher trainings in years two through five. At first glance, it might seem optimal to start all participating agencies at the same ‘baseline,’ but the structure of the funding mechanism makes such a design prohibitive due to the costs associated with implementation in each agency. By limiting training to two to three CBOs per year, we will be able to devote sufficient effort to test whether our implementation approach does in fact contribute to high fidelity implementation. Also, this randomized ‘roll-out’ implementation, or dynamic wait-listed design, has very good statistical properties, including higher power than traditional wait-listed designs [37] and less vulnerability to external, uncontrolled factors [38]. After each of the collaborating agencies completes three eight-week intervention cycles, sustainability will be studied for nine months, during which time only technical assistance will be provided, as discussed further below.

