### Delivery of the Eban II intervention

Agencies will be activated sequentially as cohorts are completed. The flow of agency participation will be as follows: year one, two agencies; year two, two agencies; year three, three agencies; year four, three agencies. All agencies will be required to complete three Eban cycles (eight weeks/cycle). In year five, three-month follow-up evaluation data collection will continue and sustainability will be studied at the agencies that complete the active phase in year four.

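### The Aim two tests on number of cycles completed have no planned variation to work with, because three cycles are required of every agency

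*Protocol article*

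**What the plan says.** All references are to the protocol article.

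- **Delivery of the Eban II intervention:** "All agencies will be required to complete three Eban cycles (eight weeks/cycle".
- **Overview of study design**, on the move to the next phase: "After each of the collaborating agencies completes three eight-week intervention cycles, sustainability will be studied for nine months".
- **Overview of study design**, on success: successful implementation is defined "as a combination of number of couples served (minimum of 18 couples per agency), three completed cycles of the intervention". The two remaining components concern fidelity and satisfaction: "delivery of the intervention with high fidelity, and high level of satisfaction with the intervention".
- **Specific aim two** sets out three steps. Step one obtains the distribution of the number of cycles completed. Step two tests the cycle count against measures of success: "two-way table chi-squares or analysis of variance will be used to evaluate the relationships between the categories of number of intervention cycles completed". Couples served, fidelity and satisfaction are given as examples of how success is measured. Step three uses regression to relate provider measures to cycles completed, adjusting for agency characteristics.
- **Specific aim two**, on dose: "An ordinal measure that reflects the number of intervention groups conducted at each agency will be created". It is to be linked to the number of cycles completed and used to test dose-response.
- **Participating agencies and staff:** "We recruited ten HIV/AIDS CBOs in Los Angeles and Alameda Counties to serve as study sites". There are therefore 10 units at agency level.

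**The concern.** The analysis depends on agencies differing in how many cycles they complete, while the design asks all of them to complete the same number. When the protocol is followed, the grouping variable has one category.

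Variation in the active phase can come only from agencies that miss the requirement. A second difficulty then appears. Success is itself defined partly by "three completed cycles of the intervention", and couples served, another component, tends to accumulate as cycles are run. An association in step two could then reflect how success was defined, and be read as a finding about implementation.

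At stake is part of the quantitative work for one of the two primary implementation aims. The randomised comparison under Aim three is not involved.

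**Working it through.** The article gives no power figure or expected result for these tests, so there is no figure to reproduce. The check is structural.

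**Inputs.** Agencies: 10. Required cycles per agency: 3. Minimum couples per agency: 18. Type I error: 0.05 (Sample size calculation and power analyses).

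**Case A: all 10 agencies complete three cycles.**

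- Variance of the cycle count: every value is 3 and the mean is 3, so the variance is 0.
- Step one: computable, but the distribution is a single point, 10 of 10 at three.
- Step two, two-way table with c success categories: df = (1 − 1) × (c − 1) = 0. ANOVA between-group df = 1 − 1 = 0. No test exists.
- Step three: if cycles is the predictor, the column of 3s is three times the intercept column, so the matrix [1, cycles] has rank 1 and the slope is not estimable. If cycles is the outcome, its total sum of squares is 0 and there is nothing to explain.
- Dose-response: the section on phase four (practice improvement) speaks of three required groups, which suggests one group per cycle. On that reading the ordinal measure is also 3 everywhere and no agency-level dose-response can be estimated.

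**Case B: k of the 10 agencies fall short.** Suppose the k agencies separate perfectly from the rest on the other variable, which is the most favourable result possible. With C(10, k) equally likely allocations, the smallest two-sided p-values are 1/C(10, k) for Fisher's exact test and 2/C(10, k) for the Mann-Whitney test, the example of a non-parametric method given under Specific aim two:

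| k | C(10, k) | Fisher | Mann-Whitney |
|---|---|---|---|
| 1 | 10 | 0.100 | 0.200 |
| 2 | 45 | 0.022 | 0.044 |
| 3 | 120 | 0.008 | 0.017 |

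At least two agencies must deviate before either test can reach 0.05. The ordinary chi-square does not rescue k = 1: the smallest expected cell count is 1 × 1 / 10 = 0.1, too small for its approximation.

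**Overlap in step two under Case B.** An agency with fewer than three cycles fails the definition of success automatically. At the minimum recruitment, couples per cycle are 18/3 = 6, so an agency that stops after two cycles at that pace has served 2 × 6 = 12, below 18. Fidelity and satisfaction are not counts and do not accumulate in this way.

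The strength of the link with couples served cannot be taken from the article. As an assumption, let agencies complete 1, 2 or 3 cycles with probabilities 0.15, 0.25 and 0.60, with 6 couples per cycle on average. The median Spearman correlation between cycles and couples served, simulated over 10 agencies with no determinant acting, is then:

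- 1.00 with no noise;
- 0.87 or 0.80 with independent noise of SD 1 or 2 couples per cycle;
- about 0.81 or 0.68 if the same SDs apply to an agency-level recruitment rate;
- 0 if agencies recruit towards 18 couples regardless of cycles.

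The range is wide and depends on the recruitment model.

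**The case against.** The strongest reply is that three cycles is a requirement and not a guarantee. Listing it as a component of success makes sense only if an agency can fail it, and looking at the distribution first, as step one does, is reasonable. That stands: shortfall is possible, and step three would then be a legitimate question about whether provider measures go with delivery. It does not supply variation that the plan can count on.

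A second reply is that cycles delivered in the sustainability phase could vary between agencies, and Specific aim two does not confine the count to the active phase. This also stands as an ambiguity. However, delivering two further cycles is part of how sustainability is defined, so a count that includes them could not be related to that outcome without the same overlap.

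A third reply is that the article does not define the groups measure, and more than one group might run within a cycle. If so, that measure could vary, and the article should say so.

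A reader might infer that all three steps are either impossible or circular. The text does not support this. Step one is always computable, step three contains no success variable, and step two overlaps only through the three-cycle component and couples served. Nor does the quantitative study of determinants return nothing. The rest of the Aim two plan and the qualitative analysis section provide for determinants of fidelity, satisfaction within and across agencies, bivariate and mixed-model analyses of sustainability, and associations among satisfaction, fidelity, retention and behavioural improvement. None of these depends on the active-phase cycle count.

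**Conclusion.** The point holds in a limited form. Sections of the article conflict: the design fixes the target at three cycles for all 10 agencies, and the analysis uses the number of cycles to distinguish agencies. With full compliance, and counting the active phase only, steps two and three cannot be estimated. The same is true of the agency-level dose-response test if a group corresponds to a cycle. With shortfall, step two is partly circular and the exact tests need at least two deviating agencies to reach 0.05.

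The structural results and the exact p-values rest only on the 10 agencies and the three-cycle requirement. The correlations with couples served rest on assumed shortfall and recruitment, and should not be quoted as the size of the problem. Because the article itself names the variable, the tests and the requirement, this is not a detail left to a fuller document. It deserves correction, but it concerns part of one implementation aim and leaves the effectiveness comparison untouched.

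**What to change.** 1. Report completion of three cycles descriptively, as the number of agencies out of 10.
2. In steps two and three, replace the cycle count with measures that can vary and are not part of the success definition. Session attendance and session completion qualify; both are listed under Implementation-focused evaluation.
3. Define dose as sessions attended (0 to 8) per couple assigned to Eban II, analyse it at couple level, and label it observational. Drop the agency-level link between groups and cycles.
4. State whether sustainability-phase cycles count. If they do, do not relate that count to the sustainability outcome it helps define.

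Time needed to finish three cycles is a less suitable substitute: the article does not list it as collected, and it is undefined for an agency that never finishes.

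The cost is revised analysis wording with no new data collection. The Trial status section says that cleaning and analysis have not commenced, so the change can still be made beforehand. The drawback is that attendance is not randomised: couples who attend more may differ in ways that also affect condom use, so the dose analysis cannot carry a causal claim.
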